## Abstract

**Background:**

Wearable devices enable continuous measurement of physical activity, sedentary behavior, sleep, and heart rate under free-living conditions. However, most validation studies rely on small, homogeneous samples; are conducted under laboratory conditions; or lack gold standard ground-truth measurements, limiting the generalizability and accuracy of derived metrics. There is a pressing need for open-access, large-scale, free-living validation datasets that include multisensor data from diverse body locations and participant demographics to aid in model development.

**Objective:**

The Oxford Wearable ECG, Activity, Circadian Rhythm, and Sleep Validation Study (OxWEARS) aims to (1) validate accelerometer-based measurement of physical behaviors across 5 body sites against annotated camera data; (2) validate measurements of sleep and sleep staging from 5 different body sites against polysomnography; (3) validate wrist-worn photoplethysmography heart rate measurements against chest-worn electrocardiogram; and (4) generate a comprehensive, annotated, and anonymized dataset for open-access research use.

**Methods:**

This cross-sectional study will recruit approximately 160 adults (aged ≥40 years) stratified by age, sex, and BMI from the Oxford BioBank. Over 3 days and 4 nights, participants will wear sensors on the wrists, chest, hip, thigh, and ankle. Ground-truth measures will be obtained from a chest electrocardiogram patch for heart rate, a first-person camera for activity annotation, an ankle-worn accelerometer for step count, and at-home polysomnography for sleep. An under-mattress sensor will collect measures of sleep, respiration rate, and bedtime, and a subjective sleep diary will also be obtained. Signals from different wear locations will be compared against the ground truth using precision, recall, *F*_1_-score, κ, and agreement metrics.

**Results:**

Recruitment commenced in November 2024, with 15 participants enrolled by May 2025. Overall, 50% of eligible adults contacted were happy to consent to the study, with excellent compliance with the protocol observed to date. Data collection is ongoing and expected to conclude in 2026, with the final annotated dataset made publicly available as soon as possible thereafter.

**Conclusions:**

The OxWEARS study will generate an openly accessible dataset containing more than 10,000 annotated hours from a stratified sample of adults. This will directly support scalable, generalizable human activity recognition efforts, while also enabling robust development and benchmarking of wearable-derived health metrics.

## Introduction

The use of wearable devices for the assessment of physical activity, sedentary behavior, and sleep allows for the quantification of 24-hour human physical behaviors without the recall and social desirability biases associated with self-reported measures [1-3]. While these behaviors are commonly measured using commercial- and research-grade devices within epidemiological studies, the accuracy of the derived metrics against gold standard ground truth is currently uncertain. To date, most activity and sleep validation studies of wearables have been of poor quality—conducted in small, homogeneous cohorts; under laboratory conditions for a single day; and often without a gold standard reference [4,5]. Additionally, most studies focus on either sleep or physical activity, resulting in a lack of ground-truth reference measures for all behaviors across the 24-hour day.

While some accelerometer models have been trained using free-living validation data, significant room for improvement exists in model generalizability and specifically in improved performance in analyzing physical activity, sedentary behavior, and sleep. For example, some validation studies have collected wrist-based accelerometer data paired with first-person camera images for behavior classification [6,7], and these methods have subsequently been adopted in large epidemiological studies for health research [8,9]. However, these data were collected in a convenience sample over a single day without deference to age, sex, and BMI [10]. Additionally, more multisensor datasets are needed to compare data collected concurrently from different wear locations, as reflected in the existing literature. For example, large datasets exist with accelerometers worn on the wrist [8,11], hip [12], and thigh [13-15]; however, there is limited evidence regarding the harmonization of physical behavior phenotypes generated from different wear locations for subsequent statistical analyses. Furthermore, combining different signals from newer devices, such as photoplethysmography (PPG) and accelerometry, may improve the detection of sleep, physical activity, and sedentary behavior by providing additional data streams for model development. Finally, in most validation studies, raw data are not published, hampering external validation efforts and method development to improve performance [4,16].

Therefore, our overarching aim is to collect a free-living validation dataset, annotating wearable sensor data with gold standard, ground-truth labeled data, for application to large-scale accelerometer datasets with linked health records.

The main aims of this study are as follows:

To validate the measurement of physical activity and sedentary behavior from accelerometers worn on the wrist, chest, waist, hip, thigh, and ankle compared with ground-truth annotations from wearable camera data.To validate the measurement of sleep and sleep staging from accelerometers worn on the wrist, chest, waist, hip, and thigh compared with gold standard polysomnography (PSG) sleep metrics.To validate the measurement of heart rate and heart rate variability from wrist-worn PPG sensors against a ground-truth chest-worn electrocardiogram (ECG) patch.To generate an anonymized dataset of annotated physical activity, sedentary behavior, sleep, and cardiac monitoring data for unrestricted use by the wider scientific community.

## Methods

### Ethical Considerations

Ethics approval was received from the University of Oxford Central University Research Ethics Committee on August 1, 2023 (R74559). Before the initiation of any study procedures, all participants were provided with an information sheet (Multimedia Appendix 1) and gave written informed consent using a digital signature platform compliant with ISO 27001 standards (E-Sign; E-Sign Ltd). Participants’ privacy is of the utmost importance to us; therefore, no identifying information will be published, and individual data will be deidentified before any data release. Participants will receive no compensation for their participation but will be provided with a nondiagnostic report on their sleep and physical behaviors during the course of the monitoring period. Conforming to current ethical frameworks [17,18], written consent to be recorded by the video camera is not required from bystanders; however, participants will be instructed to obtain verbal permission from and provide an explanation of the device to family members, cohabitants, workplace managers or supervisors, or other people in settings where a reasonable expectation of privacy exists. This approach was considered reasonable. A script and information card will be provided for use if participants are questioned by members of the public. While we obtain consent, we will also ask participants to sign a privacy agreement for the recording of video for this study in public and private settings (Multimedia Appendix 2). Participants will be instructed on how to cover the camera or pause data collection at any time when they need privacy or feel uncomfortable or unsafe. Examples of this include using the bathroom (in public or private), using public changing rooms, interacting with unrelated children, or working in contexts where intellectual property must be protected. In line with the ethical framework established by Kelly et al [17], participants can request the removal of any unwanted or sensitive footage potentially caught on camera. Privacy concerns related to the wearable camera data are of critical importance. Therefore, raw video footage will never be released, and any examples used (such as for annotator training) will be confined to the University of Oxford research team. All data will remain on University of Oxford servers.

### Data Deidentification

In line with previous research, no wearable camera data will be shared outside of the University of Oxford [7]. Each participant will be assigned a unique study identifier, which will be used to label all associated raw data files. Because participants could potentially be deidentified based on combined age, sex, and BMI, we will report only the subgroup to which each participant belongs, as described earlier. Finally, the start dates of the raw data will be randomized, and time stamps will also be shifted by a small random amount so that they do not reflect the true dates and times of the data. Similar steps have been used previously to ensure deidentification of participants taking part in studies [7].

### Recruitment

OxWEARS is a cross-sectional study and will recruit a target sample of 160 participants from the Oxford BioBank [19]. A sample size of 160 will provide 80% power to detect a difference of 0.05 in Cohen κ score (effect size=0.25, assuming an SD of 0.25 from previous studies [20]) between 3 age groups using a fixed effects one-way ANOVA test (α=.05). The Oxford BioBank is a population-based cohort of approximately 9000 participants aged 25 to 55 years recruited in Oxfordshire, United Kingdom, from 1999 onward. Inclusion and exclusion criteria for this study are presented in Textbox 1. Recruitment will target the creation of a final study cohort evenly balanced by sex, age (40‐54 years, 55‐64 years, and ≥65 years), and BMI (18.5‐25 kg/m^2^, 25‐30 kg/m^2^, and >30 kg/m^2^). The distribution of invitations will be regularly rebalanced to achieve 13 to 14 participants in each subgroup by the end of the study.

Textbox 1.Inclusion and exclusion criteria.

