## Results

To date, 150 participant information sheets have been sent to members of the Oxford BioBank database. Of these, 30 (20%) have expressed interest, and 15 (50% of those expressing interest) have provided consent. Common reasons for not progressing to consenting so far include ineligibility due to occupation (teacher or health care worker), requests to be contacted at a later date, and inability to make contact with the participant. The first participant consented and completed data collection in November 2024. As of May 2025, we had enrolled 15 participants, with 12 (80%) completing the monitoring period with excellent adherence to the protocol. Data collection is expected to be completed in 2026.

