Strengths of this study include the large, stratified sample to create a more heterogeneous, multimodal dataset; the inclusion of ground-truth measures of physical activity, sedentary behavior, sleep, and heart rate; and the planned release of the data to the wider research community. One limitation of this study is the lack of dietary or cognitive data, meaning certain behaviors cannot be linked to physiological metrics, for example, postmeal sedentariness and heart rate variability. Future work could explore the capture of these behaviors to provide additional context to physiological responses. Furthermore, despite recruiting a large sample size in comparison to existing device validation studies, subgroup analyses may be challenging when assessing algorithm performance. However, due to our methodology, it would be possible for these data to be combined with other datasets (eg, Capture-24) to increase the statistical power of these comparisons in the future. Finally, although we recruit a sample stratified by age, sex, and BMI, our sample does not include younger adults aged <40 years, those with chronic illnesses, or non-English speakers. Therefore, the results will only be applicable to healthy adults with a demographic profile similar to the recruited participants. Future work should strive to include representativeness of these characteristics in addition to improving representativeness from low- and middle-income countries to assess generalizability of machine learning algorithms trained on this dataset. Despite these limitations, we anticipate that the study’s strengths will make the resulting dataset the largest and most comprehensive open-access validation dataset worldwide.

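### The sample-size inputs contradict each other: a κ difference of 0.05 with an SD of 0.25 is not an ANOVA effect size of 0.25, and the stated 80% power follows only from the latter

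*Protocol article*

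**What the plan says.** The sample-size justification is one sentence in Methods, Recruitment, of the protocol article. The target is stated as follows: the study "will recruit a target sample of 160 participants from the Oxford BioBank". The power claim is that this number gives "80% power to detect a difference of 0.05 in Cohen κ score (effect size=0.25, assuming an SD of 0.25", with the SD attributed to earlier studies. The test named is a fixed-effects one-way ANOVA comparing three age groups at α=0.05. The same paragraph aims for a cohort evenly balanced by age, which gives about 53 per age group at 160. The type of effect size is not named, and the assumed pattern of the three group means is not given.

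**The concern.** The sentence gives a difference, an SD and an effect size. Any two of these, with a pattern of means, should determine the third. Even as a plain ratio, 0.05/0.25 is 0.20, not 0.25. The ANOVA effect size f is smaller again than the ratio of the largest difference to the SD, because it uses the SD of the group means and not their range.

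This is the only justification of sample size in the article, and agreement across age, sex and BMI subgroups is a declared comparison for heart rate (Data Processing and Analysis). A reader who takes the sentence at face value would treat a null age comparison as good evidence against a κ difference of 0.05. If the stated difference and SD are both right, that inference would not be safe.

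**Working it through.** **Inputs**, all from Methods, Recruitment: N=160; k=3 equal age groups; α=0.05; stated power 80%; difference 0.05 κ; SD 0.25, taken as the within-group SD of participant-level κ; effect size 0.25, taken as Cohen's f because the test is a one-way ANOVA.

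**Formulas.** f = σ_m/σ, where σ_m is the SD of the three group means (divisor 3) and σ is the within-group SD. Power is the upper tail of a noncentral F with 2 and 157 degrees of freedom and noncentrality λ = f²N.

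**Step 1: reproduce the plan's figure.** With f=0.25, λ = 0.0625 × 160 = 10 and power is 80.8%. The smallest N for 80% is 158. The pairing of 160 with 80% therefore reproduces, from the effect size alone.

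**Step 2: derive f from the stated difference and SD.**
- Largest gap 0.05, means equally spaced (0, 0.025, 0.05): σ_m = 0.05/√6 = 0.0204, and f = 0.0204/0.25 = 0.082.
- Largest gap 0.05, two groups at one extreme (0, 0, 0.05): σ_m = 0.05 × √2/3 = 0.0236, and f = 0.094.
- Gap of 0.05 between adjacent groups (0, 0.05, 0.10): σ_m = 0.10/√6 = 0.0408, and f = 0.163.
- The ratio 0.05/0.25 used directly as f (0.05 treated as the SD of the means): f = 0.20.

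**Step 3: power under each reading.**

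| Reading of 0.05, with SD 0.25 | f | λ at N=160 | Power at N=160 | N for 80% |
|---|---|---|---|---|
| Largest gap, equally spaced | 0.082 | 1.07 | 13.7% | 1,449 |
| Largest gap, two groups at one extreme | 0.094 | 1.42 | 16.9% | 1,087 |
| Gap between adjacent groups | 0.163 | 4.27 | 43.2% | 365 |
| 0.20 taken as f | 0.200 | 6.40 | 60.5% | 244 |

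Reading the stated effect size of 0.25 as a standardised difference d does not help: f is then 0.102 to 0.118 and power 19.1% to 24.3%. As a cross-check, a two-sided pairwise z test with about 53 per group, difference 0.05 and SD 0.25 has 17.7% power.

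**Step 4: solve for what would make the sentence consistent.**
- Keep f=0.25 and SD 0.25: σ_m = 0.25 × 0.25 = 0.0625. The largest difference is 0.0625 × √6 = 0.153 if the means are equally spaced, or 0.0625 × 3/√2 = 0.133 if two groups share one extreme.
- Keep f=0.25 and a largest difference of 0.05: the SD must be 0.0204/0.25 = 0.082 (equally spaced) or 0.0236/0.25 = 0.094 (two groups at one extreme).

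**Step 5: precision at N=160, conditional on SD 0.25.** The 95% half-widths are:
- overall mean κ: 1.96 × 0.25/√160 = 0.039
- one age group: 1.96 × 0.25/√53.3 = 0.067
- pairwise age difference: 0.067 × √2 = 0.095

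**The case against.** The strongest reply is that the effect size is itself a stated input and delivers the stated power. That is right. It means the fault is a mismatch among inputs, and one cannot say outright that the study has 14% to 17% power. A reader might infer that stronger statement, but it requires the difference and the SD both to be correct and 0.05 to be the largest gap. The article shows neither the source of the SD nor the pattern of means. If the SD or the difference is the slip, the power figure could stand for the corrected input.

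A reader might also infer from the Results section, which reports "12 (80%) completing the monitoring period with excellent adherence to the protocol", that only 80% of recruits will be evaluable and that power should be cut accordingly. The article does not support this. It is a snapshot taken while data collection was under way, and nothing says that the other three withdrew or gave unusable data.

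Nor does the Discussion contradict the power claim. Its remark that "subgroup analyses may be challenging when assessing algorithm performance" names no subgroup and may refer to the finer age-by-sex-by-BMI cells. It is a partial caution, though it does not correct the figure.

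The paragraph also asks for 13 to 14 participants in each subgroup. If that means all 3 × 2 × 3 = 18 cells, the total is 234 to 252, not 160. That discrepancy needs its own clarification. It does not repair a sentence that claims 80% power at 160, and on the largest-gap reading those totals would still give only about 18% to 25%.

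Finally, the stated primary aim is to build a dataset, and the ANOVA is mentioned only in the sample-size sentence. No primary conclusion depends on it. That limits the consequences, but this is still the sole justification offered for 160.

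**Conclusion.** The sentence is wrong as written: a κ difference of 0.05, an SD of 0.25 and an effect size of 0.25 cannot all be true for a three-group ANOVA. The 80% at 160 belongs to f=0.25. With the stated difference and SD, power at 160 is about 14% to 17% if 0.05 is the largest gap (the natural reading), about 43% if it is the gap between adjacent groups, and about 60% if 0.20 is used as f. None of these readings reaches 80%. The results assume equal age groups, 160 analysed participants and a common within-group SD. Which of the three inputs is misstated cannot be settled from the article, so each power figure is conditional on the stated difference and SD.

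**What to change.** Identify and correct the inconsistent input, then restate the sentence, naming the effect size as Cohen's f and giving the assumed pattern of means.

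- **If SD 0.25 is right:** say that 160 analysed participants in three equal age groups give about 80% power for f=0.25, which corresponds to a largest difference between age-group mean κ of about 0.13 (two groups at one extreme) to 0.15 (equally spaced means).
- **If 0.05 is the intended largest difference:** give the source that supports an SD of about 0.08 to 0.09.

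If precision is added, state it as conditional on the SD. At SD 0.25 the 95% half-widths are about ±0.04 for the overall mean κ, ±0.07 per age group and ±0.095 for a pairwise age difference. All would shrink in proportion with a smaller SD.

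The cost is one reworded sentence, with no extra participants and no change of design. If SD 0.25 stands, the detectable difference becomes less favourable than the one now printed.

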### Ground-Truth Physical Behavior Data Collection

To obtain ground-truth data on everyday activities, participants will wear a first-person perspective video camera (MIUFLY) during waking hours for 3 days, mirroring procedures from prior studies using first-person image capture to annotate physical activity and sedentary behavior [7,21]. In this study, a wearable camera is worn by the participant via a chest harness, neck mount, clip, or lapel and continuously records video during participant waking hours. Previous automated camera studies of this nature have reported wear time compliance of more than 80% [22,23]. No audio is captured by the camera, and all footage is encrypted on the device so that only the research team can download and view the video. Participants will be instructed on how to cover the camera or pause data collection at any time when they desire privacy or feel uncomfortable or unsafe. Examples of this include using the bathroom (public or private), public changing rooms, interacting with unrelated children, or working in contexts where intellectual property must be protected.

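### An age comparison by one-way ANOVA on raw Cohen κ mixes sensor accuracy with activity mix and leaves unused the sex and BMI factors the study balances on

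*Protocol article*

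**What the plan says.** The Recruitment section states: "A sample size of 160 will provide 80% power to detect a difference of 0.05 in Cohen κ score", with "effect size=0.25, assuming an SD of 0.25 from previous studies", compared "between 3 age groups using a fixed effects one-way ANOVA test" at α = 0.05. This is the only between-group significance test in the article, and it appears there as the basis for N.

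The same section states: "Recruitment will target the creation of a final study cohort evenly balanced by sex, age" and BMI category, with invitations rebalanced during the study to hold that balance.

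The Data Processing and Analysis section names no ANOVA. It anticipates precision, recall, F1-score, κ and accuracy for all comparisons with ground-truth labels, plus bias measures and Bland-Altman plots for summary metrics. For heart rate only, it plans comparisons across age, sex and BMI subgroups. Nothing in the article says that κ will be standardised for activity mix when age groups are compared.

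On filming, participants are told how to "cover the camera or pause data collection at any time when they desire privacy or feel uncomfortable or unsafe". The examples given include work where intellectual property must be protected.

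**The concern.** κ corrects observed agreement for chance agreement, and chance agreement depends on the share of time spent in each class. Two groups measured equally well can therefore have different κ. The strata are 40-54, 55-64 and ≥65 years, and activity mix may well differ between them. The hours filmed may differ too: the camera can be paused in some work settings, Textbox 1 restricts several occupations, and the Results section lists occupation among the common reasons for not reaching consent. The article gives no data by age on any of this, so the link to age is a plausible assumption.

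At stake is interpretation. An age difference in κ could be read as a method working less well in older adults when accuracy per behaviour is unchanged, or a real loss of accuracy could be hidden by a change in mix.

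The second matter is efficiency. Sex and BMI category are recruitment factors and are already recorded, yet a one-way test leaves whatever variation they explain in the error term.

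**Working it through.** **1. The plan's own figure.** Inputs from Recruitment: N = 160, 3 groups, effect size 0.25, α = 0.05. Read as Cohen f, the noncentrality is N × f² = 160 × 0.0625 = 10, on 2 and 157 degrees of freedom. Power is 80.8%, and the smallest N for 80% is 158. The stated N reproduces.

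**2. κ at fixed accuracy.** For a two-class label with prevalence p, sensitivity Se and specificity Sp:
- observed agreement po = p·Se + (1−p)·Sp
- predicted-positive share q = p·Se + (1−p)(1−Sp)
- chance agreement pe = p·q + (1−p)(1−q)
- κ = (po − pe)/(1 − pe)

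The article gives no Se, Sp or activity mix, so all values are assumed. With Se = Sp = 0.90, po is 0.90 throughout:

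| p | q | pe | κ |
|---|---|---|---|
| 0.10 | 0.18 | 0.756 | 0.144/0.244 = 0.590 |
| 0.20 | 0.26 | 0.644 | 0.256/0.356 = 0.719 |
| 0.30 | 0.34 | 0.564 | 0.336/0.436 = 0.771 |
| 0.50 | 0.50 | 0.500 | 0.400/0.500 = 0.800 |

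From 20% to 30% the shift is 0.771 − 0.719 = 0.052; from 10% to 20% it is 0.719 − 0.590 = 0.129.

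**3. How far this depends on the assumptions.**
- Se 0.80, Sp 0.90: κ is 0.608 at 15% and 0.534 at 10% (shift 0.074), but 0.693 at 30% and 0.706 at 40%.
- Se 0.85, Sp 0.95: κ is 0.758 at 15% and 0.706 at 10% (shift 0.052), but 0.808 at 30% and 0.800 at 50%.
- An assumed three-class waking confusion matrix: κ falls from 0.650 to 0.616 as sedentary time rises from 58% to 74%, and to 0.586 at 80%.
- An assumed four-class matrix that includes sleep: κ moves only from 0.771 to 0.779.

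A shift of 0.05 or more is thus possible, mainly for less common behaviours, and its size and direction depend on the label set.

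**4. Would the ANOVA detect it?** With the stated SD of 0.25, a range of 0.05 is 0.05/0.25 = 0.20 SD. Over three groups, f = 0.20 × √(1/6) = 0.082 for evenly spaced means, or 0.20 × √2/3 = 0.094 if one group differs. At N = 160 the test rejects in 14% to 17% of studies. With assumed prevalences of 15%, 12% and 9% in the three age groups, the range in κ is 0.069 to 0.096 (the two Se/Sp pairs in step 3), and the test rejects in 23% to 40%, against a nominal 5%.

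**5. Adding sex and BMI.** Main effects use 1 + 2 = 3 degrees of freedom, leaving 2 and 154. If they explain a share R² of the residual variance (assumed), noncentrality becomes 10/(1 − R²):

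| R² | Noncentrality | Power |
|---|---|---|
| 0 | 10.0 | 80.7% |
| 0.05 | 10.5 | 82.8% |
| 0.10 | 11.1 | 84.9% |
| 0.20 | 12.5 | 89.0% |

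These powers are at f = 0.25, the effect size that reproduces N, not at a κ difference of 0.05 with SD 0.25.

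**The case against.** The strongest objection is that the ANOVA is a powering assumption and not the declared analysis. The analysis section does not mention it, the article is condensed, and the final model may sit in a plan that is not shown. This stands: the article does not commit the study to an unadjusted final comparison. The point therefore concerns the one test that is stated and how any age comparison should be done.

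It is also true that recall is already planned, and class-specific recall does not depend on class prevalence. That supplies part of the remedy. But recall is not tied to the age comparison, κ is the quantity on which N rests, and precision, F1-score and, in general, overall accuracy also move with the mix.

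Two stronger readings are tempting:
- A reader might infer that leaving out sex and BMI can itself create an age effect. The Recruitment section aims to balance both against age, and with that balance the age contrast is unbiased.
- A reader might infer that a 0.05 artefact would usually be declared significant. At the stated SD it would not (step 4).

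Finally, the pause instruction applies to everyone, and nothing in the article links pausing to age.

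**Conclusion.** The point holds as a low-cost improvement to the stated test. Raw κ is not a clean measure of accuracy across groups with different activity mixes. A shift of about 0.05 at identical sensitivity and specificity can be shown, but only under assumed mixes, and it is much smaller for some label sets. Omitting sex and BMI costs precision only: nothing material if they explain no variance, and about 4 to 8 percentage points of power at f = 0.25 if they explain an assumed 10% to 20%. The documents do not show that any age effect will be spurious.

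**What to change.** For any comparison between age groups, replace the one-way ANOVA with a linear model containing age group, sex and BMI category, and report the age effect from that model.

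Beside raw κ, report one measure not driven by prevalence: class-specific recall (already planned), balanced accuracy, or κ recomputed after reweighting each participant's confusion matrix to the pooled class distribution. State that an age difference in κ will be interpreted as a difference in accuracy only if that measure agrees.

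The cost is 3 degrees of freedom, one more table and a short piece of code on confusion matrices that the planned metrics already require. Participants with little or no time in a class will have unstable or undefined recall for it, so a rule for those cases is needed.

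### The quota of 13–14 participants per subgroup does not fit a target of 160 spread over 18 sex × age × BMI subgroups; 160 gives 8–9 in each

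*Protocol article*

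**What the plan says.** Three statements in the Recruitment section bear on the point.

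- **Total.** The study "will recruit a target sample of 160 participants from the Oxford BioBank". The abstract agrees: "This cross-sectional study will recruit approximately 160 adults".
- **Strata.** "Recruitment will target the creation of a final study cohort evenly balanced by sex", and likewise by three age bands (40–54, 55–64, 65 and over) and three BMI bands (18.5–25, 25–30, above 30 kg/m²).
- **Quota.** "The distribution of invitations will be regularly rebalanced to achieve 13 to 14 participants in each subgroup by the end of the study".

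The Data Deidentification section shows what a subgroup is. It is concerned that age, sex and BMI taken together could identify someone, and its safeguard is that "we will report only the subgroup to which each participant belongs", with a reference back to the subgroups already described. Each participant thus belongs to one subgroup, defined by the three factors jointly. The Metadata Description fits this: age category, sex and BMI category are released for each participant.

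**The concern.** The total, the strata and the quota cannot all hold. Crossing the three factors gives 18 subgroups, and 160 people cannot put 13–14 in each.

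This is more than a loose descriptive figure, because invitations are to be redistributed repeatedly in order to reach it. A team that treats it as the target for each subgroup will not regard one holding 9 people as full, although 9 is already its even share of 160. It may then recruit beyond 160, or stop at 160 with some subgroups near 13–14 and others short.

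The figure also tells readers, and future users of the open dataset, how many people to expect in each subgroup. On that count it promises more than the design can deliver. The same figure bears on the deidentification argument, since subgroups of 8–9 give less cover than subgroups of 13–14.

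**Working it through.** **Inputs** (all from the Recruitment section unless noted): N = 160; sex 2 levels; age 3 bands; BMI 3 bands; quota 13–14 per subgroup. For the power check: one-way fixed-effects ANOVA, 3 age groups, effect size 0.25, α = 0.05, 80% power.

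**Step 1. Does the quota follow from 160 under any reading of subgroup?** Average size = 160 / number of groups; total needed = number of groups × 13 to number of groups × 14.

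| Reading | Groups | 160 / groups | Total needed for 13–14 each |
|---|---|---|---|
| Sex | 2 | 80 | 26–28 |
| Age, or BMI | 3 | 53.3 | 39–42 |
| Sex × age, or sex × BMI | 6 | 26.7 | 78–84 |
| Age × BMI | 9 | 17.8 | 117–126 |
| Sex × age × BMI | 18 | 8.9 | 234–252 |
| A 12-cell grid (not described in the article) | 12 | 13.3 | 156–168 |

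The quota is not reproduced by any grouping of the stated factors. It is reproduced only by 12 cells, for example if one of the three-level factors had been counted as two levels (2 × 2 × 3). That origin is an inference; the article does not state it.

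**Step 2. Size of the mismatch on the crossed reading.**

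- Excess over target: 234 − 160 = 74 and 252 − 160 = 92, that is 74/160 = 46% to 92/160 = 58%.
- Quota against even share: 13/8.89 = 1.46 and 14/8.89 = 1.58, so roughly 50% too many per subgroup.
- Implied age band: each band spans 2 × 3 = 6 subgroups, so the quota implies 6 × 13 = 78 to 6 × 14 = 84 per band, against 160/3 = 53.3.

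**Step 3. Could an allowance for dropout explain it?** The article states none. To end with 160 after filling every subgroup to 13–14, the completion rate would have to be 160/252 = 63% to 160/234 = 68%. The Results section reports 12 of 15 (80%) having completed so far. Even if the other three are all counted as losses, 160/0.80 = 200 recruits, and 200/18 = 11.1 per subgroup, still below 13.

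**Step 4. Does the total of 160 depend on the quota?** Power comes from the noncentral F distribution with 2 and N − 3 degrees of freedom and noncentrality N × 0.25². At N = 160 it is 80.8%, and the smallest N reaching 80% is 158. The total therefore stands on the ANOVA inputs as stated. Whether a κ difference of 0.05 with SD 0.25 corresponds to an effect size of 0.25 is a separate question and is not assessed here.

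**Step 5. What 160 does deliver.** 16 subgroups of 9 and 2 of 8 make 144 + 16 = 160, so 8–9 per subgroup is attainable, with about 53 per age band, 53 per BMI band and 80 per sex.

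**The case against.** The arithmetic is hard to dispute, but its consequences can be overstated.

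- **Balance.** A reader might infer that following the quota must wreck the even balance. The article does not support that. Rebalancing sends invitations towards under-filled subgroups. If it works, the subgroups rise together, and stopping at 160 leaves about 9 in each whatever ceiling was written down. Uneven subgroups are a risk that arises if rebalancing is imperfect or subgroups are filled one after another. This objection stands.
- **Power.** A reader might infer that the sample size is invalid. It is not: Step 4 recovers 160 without the quota. This stands too.
- **Precision within subgroups.** A reader might compare the precision of κ in a subgroup of 9 with that in one of 13–14. The article plans no estimate within the 18 crossed subgroups. The power statement concerns age groups, and the comparisons across age, sex and BMI in Data Processing and Analysis read naturally as comparisons on each factor. The Discussion already concedes that subgroup analyses may be difficult. No harm of this kind is claimed.
- **Which figure is wrong.** The article does not say whether the quota, the strata or the total is the slip. This stands, and the fix has to allow for it.
- **Little has happened yet.** Only 15 people were enrolled by May 2025, so no great distortion can have built up by then. That is true, but it is a reason to correct the figure early, not a reason to leave it.

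None of these points reconciles the three stated numbers. The word approximately in the abstract cannot absorb 74–92 extra people.

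**Conclusion.** The quota is wrong as written. With the stated strata, 160 participants give 8.9 per subgroup, while 13–14 per subgroup needs 234–252. The declared subgroup size is about 50% above what the design provides (46–58%). The practical consequence is a risk of overshooting 160 or of finishing with uneven subgroups, together with a misleading expectation for readers. It is not a demonstrated loss of balance, and it does not invalidate 160 as the sample size.

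The conclusion rests on reading a subgroup as one sex × age × BMI combination, which the Data Deidentification section supports. It does not depend on that reading alone, since no other grouping of the stated factors gives 13–14 either. That the quota came from a 12-cell grid is plausible but unstated.

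**What to change.** Keep the target of 160, which is the figure the power statement supports. Replace the quota with 8 to 9 participants in each of the 18 sex × age × BMI subgroups, adding that this amounts to about 53 per age band, 53 per BMI band and 80 per sex. Set the invitation tracker to that figure.

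If a 12-subgroup scheme was intended, leave the quota and correct the description of the strata instead. Raising the total to 234–252 would also make the numbers agree, but nothing in the power statement calls for it.

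The cost is one reworded sentence and a change to the tracker. The downside is that the declared subgroup size falls from 13–14 to 8–9, and the deidentification argument should be reread with the smaller number in mind.
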